### Dropout and discontinuance

Dropout cases in the present study include; 1) participants who have not undergone an annual health checkup after enrollment, and 2) participants who have lost contact with the study team. Discontinuous cases are defined as; 1) participants who have developed adverse events that make continuance impossible, 2) participants who request to discontinue, 3) participants who are judged inappropriate for continuing the study by the project leader for various reasons.

### Data management

Data management is outsourced to CIMIC Co., Ltd., Japan, a contract research organization offering clinical research management services. All data obtained in the study will be stored in de-identified forms in the data management center and used in conformity with the study aims only. The project leader (HK) has overall responsibility for management of the study data.

### Blinding

Study participants and the staff members are not blinded to the study arm status. Analysts who perform final data analysis will be blinded.

### Sample size

The present study is likely to observe a significantly longer diabetes-free period in the intervention than in the control arm. Thus, the null hypothesis is that the diabetes-free period in the intervention arm is the same as that in the control arm. The sample size(S) needed is calculated using the formula [34,35]; S = (1 + [cluster size − 1] × ICC) × N, where N represents the sample size required when study subjects are randomized individually, and ICC represents an intra-cluster coefficient [36]. Based on the available prospective data from Japanese population the yearly incidence of diabetes among high-risk group varies between 2 and 7% [37,38]. When calculated on the assumption that the annual incidence of diabetes is 4% in the control arm and the intervention reduces the incidence by 50%, N will be 1100 with an alpha of 5% and a power of 90% according to Shoenfeld & Richter [34]. When the ICC and the cluster size (number of individuals in each cluster) are assumed to be 0.02 and 60, S and the number of clusters will be 2398 and 40, respectively. Assuming that the dropout rate is 30%, 3426 subjects are needed. On the assumption that 1) the prevalence of high-risk individuals in each cluster is 10%, and 2) 30% of eligible subjects consent to participate in the study, the total number of health checkup examinees required would be approximately 114,200, and the number of health checkup examinees in each cluster will be approximately 2900. For descriptive analyses of the diabetes-free duration, the Kaplan-Meier method is used.

### Statistical analyses

The analyses are done using Statistical Package for Social Science software version 19.0 (SPSS Inc., Chicago, IL, USA) or SAS version 9.3 (SAS Inc., Cary, NC, USA). The analysis will be done on an intention to treat basis. Survival curves for the development of diabetes will be estimated by the Kaplan–Meier method. The log rank test will be also conducted. We will take into account the clustering effect in the main outcome analysis and sub-analysis using the LWA model (Lee, Wei and Amato) [39-41]. Cox regression analysis will be used to calculate the unadjusted and adjusted HRs and 95% CIs for arm and risk factors. In multivariable Cox analysis, all significant variables selected for the univariate analysis will be used with the criterion of p<0.1. Student's t-test (or Mann-Whitney U-test according to the frequency distribution of the variable) will be used to compare the means (or the distribution) of the two study arms for continuous variables. Chi-square test or chi-square for trend will be used to compare proportions for categorical variables. We do not adjust for the clustering effect for analysis of the secondary outcome. Those cases with missing data will be simply omitted in the relevant analysis. A p value less than 0.05 is considered significant.

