## Results

Forty-three groups, formed from 17 health care divisions at companies or communities across the country, were randomly assigned to a control arm (21 groups) or an intervention arm (22 groups) between March 2007 and February 2008. Figure 2 shows the flow of recruitment of study subjects through annual health checkups. Approximately 230, 000 individuals (male 85%) underwent health checkups by those 43 groups in 2006. Among them, 14,473 subjects (7494 in the control and 6979 in the intervention arm) met the inclusion criteria and received an invitation letter to participate in the study. As a result 1643 subjects from the control and 1491 subjects from the intervention arm consented to participate. Finally, 2897 subjects were enrolled, with 1524 in the control and 1336 in the intervention arm. The overall consent rate of the study was approximately 20% with no difference between the study arms. Among the 2897 subjects, 57 subjects (20 in the control and 37 in the intervention arm) were enrolled with CPG of 118-143 mg/dL 6.6-7.9 mmol/L). As shown in Figure 2, those subjects are not included for the main outcome analysis. The remaining 1504 in the control and 1336 in the intervention arm will be followed up for the development of diabetes (primary outcome). The median (interquartile range) of the group size in the control arm before and after screening for eligibility was 301 (200-442) and 61 (35-88), respectively and those in the intervention arm was 313 (158-587) and 60 (41-94), respectively. There is no difference in group size between arms. In one group in the control and two groups in the intervention arm no participants were enrolled with FPG. Those three groups were not included in the calculation of cluster size. The number of company settings, community settings, and mixed settings in the intervention arm were 16, 3, and 1, respectively. The number of company settings, community settings, and mixed settings in the control arm were 15, 3, and 2, respectively. There were no differences between the arms in the characteristic of the participants in terms of age, sex ratio, FPG levels, BMI, and the prevalence of obesity (Table 2). No difference was found in the prevalence of the Metabolic Syndrome, either (Table 3). All follow-up data will be collected by winter 2012.

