### Cluster randomization

In recently reported lifestyle intervention studies, both individual randomization and cluster randomization [42,43] have been used. The cluster randomization design has the advantages of administrative convenience, ease of obtaining the cooperation of investigators, enhancement of subject compliance, and avoidance of treatment contamination. Since study subjects in this trial are employees of the same workplaces or inhabitants of the same communities, we chose cluster randomization to avoid diluting the effect of the intervention. The contamination could occur with individual randomization e.g. by control subjects receiving part of the intervention in a shared environment. Generally, cluster randomized trials, are susceptible to a range of methodological problems including selection bias [18]. Selection bias can be avoided by recruiting and enrolling the study subjects into the study before the groups are allocated to the study arms [44]. In our study design, however, the study subjects were recruited after the clusters were randomly allocated to the intervention or control arm. The reason for nor recruiting and enrolling subjects before randomization was that it was not practical due to the nature of the intervention, in which it takes too long to recruit individuals first. The individuals or the recruiters were not blinded to the allocation status. Careful attention should be paid to the likelihood of selection bias in our sample based on the cluster sizes between the two arms and comparison of the participants.

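### The adjusted hazard ratio takes its covariates from a univariate p<0.1 screen with no baseline factor or stratum forced in, and the plan does not say which hazard ratio is the main estimate

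*Protocol article*

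**What the plan says.** The Statistical analyses section plans Kaplan-Meier curves, a log-rank test and the following treatment of clustering: "We will take into account the clustering effect in the main outcome analysis and sub-analysis using the LWA model (Lee, Wei and Amato"). No covariates are named for that model. It then adds: "Cox regression analysis will be used to calculate the unadjusted and adjusted HRs and 95% CIs for arm and risk factors". For the adjusted version the rule is that "all significant variables selected for the univariate analysis will be used with the criterion of p<0.1". No candidate list is given and no variable is said to be forced in. The strata described under Randomization (seven, five and three in the three recruitment periods) are not mentioned in the analysis.

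The Sample size section states that "the null hypothesis is that the diabetes-free period in the intervention arm is the same as that in the control arm", which is a comparison of the arms without covariates.

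On recruitment, the Discussion (Cluster randomization) says that "the study subjects were recruited after the clusters were randomly allocated to the intervention or control arm" and that "The individuals or the recruiters were not blinded to the allocation status". The response it offers is a comparison of the arms: "Careful attention should be paid to the likelihood of selection bias in our sample based on the cluster sizes between the two arms", together with a comparison of the participants. The Results report that "There were no differences between the arms in the characteristic of the participants in terms of age, sex ratio, FPG levels, BMI" and prevalence of obesity.

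**The concern.** A screen on the outcome data lets the trial's own results decide which variables the adjusted HR is conditioned on. The covariate set is then unknown until the data are analysed, and the reported confidence interval takes no account of the selection. Because an HR generally changes with the covariates in the model, even under perfect balance, the quantity being estimated also varies with what passes.

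This matters more here than in an individually randomised, concealed trial. Participants joined after their cluster's allocation was known, so imbalance in prognostic factors is a design risk that the article itself acknowledges. Adjustment for measured baseline factors is one analytic safeguard, and the adjusted HR is the only planned arm estimate described as having it. The article ties its covariates to a p-value and does not say whether this HR or the unadjusted one carries the conclusion. If the two differ, the choice between them would be open after the results are seen.

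**Working it through.** **1. The plan's own figures.** The covariate rule has no figure of its own, so I first checked the sample size that supplies the event counts. With Freedman's formula, HR 0.5, two-sided 5% and 90% power: events = (1.960 + 1.282)² × (1.5/0.5)² ≈ 95. The mean three-year risk at 4% and 2% a year is (0.1153 + 0.0588)/2 = 0.0870, so N = 95/0.0870 ≈ 1092. Treating 4% and 2% as hazards gives 1109. Both agree with the stated 1100. Then (1 + 59 × 0.02) × 1100 = 2398 and 2398/0.7 = 3426, as stated.

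**2. Expected events in the enrolled sample.** With 1504 control and 1336 intervention participants (Results) and the planning rates: 1504 × (1 − 0.96³) + 1336 × (1 − 0.98³) = 173.4 + 78.6 ≈ 252. With the planned 30% dropout: 252 × 0.7 ≈ 176.

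**3. Chance that a covariate passes p<0.1.** For a covariate in SD units, z ≈ √events × ln(HR per SD), and the chance of passing is Φ(z − 1.645) + Φ(−z − 1.645). The HRs per SD are assumptions, and clustering is ignored.

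| Assumed HR per SD | 176 events | 252 events |
|---|---|---|
| 1.10 | 35% | 45% |
| 1.15 | 58% | 72% |
| 1.20 | 78% | 89% |
| 1.30 | 97% | 99% |
| 1.50 or more | about 100% | about 100% |

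A factor with log HR 0.7 per SD (HR about 2) has z = 0.7 × √176 ≈ 9.3 to 0.7 × √252 ≈ 11.1. It would almost surely pass, provided it is a candidate.

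**4. What imbalance does to the unadjusted HR.** Three of the 43 groups enrolled nobody with FPG, so mean cluster size is 2840/40 = 71. With ICC 0.02 the design effect is 1 + 70 × 0.02 = 2.4. The SE of the standardised baseline difference is √(4 × 2.4/2840) = 0.058 SD, so one to two SEs is 0.06 to 0.12 SD. With log HR 0.7 per SD, the log HR for arm shifts by 0.7 × 0.058 = 0.041 to 0.7 × 0.116 = 0.081, about 4% to 8%. The plan's own design effect of 2.18 gives SE 0.055 and shifts of 0.039 to 0.078, essentially the same. The ICC was assumed for the diabetes outcome and is borrowed here for a covariate. Allocation within divisions could make the SE smaller. The SE covers chance imbalance only, so selective recruitment could add to it.

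**5. Screened, fixed and unadjusted models compared.** Simulation with 2840 participants, 400 runs, true arm HR 1.0 and no clustering. Assumed: one strong factor (HR 2.0 per SD), one weak factor (HR 1.12 per SD) and six null covariates. The strong and weak factors were both shifted between arms by 0, 0.1 or 0.2 SD. Arm was always in the model and both factors were candidates.

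| Model | Mean arm HR (0 / 0.1 / 0.2 SD) | Rejection rate at 5% |
|---|---|---|
| Unadjusted | 1.00 / 1.08 / 1.17 | 3.5% / 10% / 33% |
| Screened p<0.1 | 1.00 / 1.00 / 1.00 | 3.0% / 3.5% / 4.0% |
| Fixed covariates | 1.00 / 1.00 / 1.00 | 3.2% / 3.5% / 4.0% |

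The screen kept the strong factor in every run and the weak one in 57% to 67% of runs. Losing the weak factor costs little: ln(1.12) × 0.116 = 0.013, about 1.3% on the arm HR.

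**The case against.** The strongest reply is that nothing confirmatory rests on the screen. The null hypothesis, the log-rank test, the LWA analysis and the unadjusted HR do not use it, and the screened model also serves a risk-factor analysis, where screening is common. The rule and its threshold are stated in advance, the final analysts are blinded (Blinding), and a candidate list is detail that an article may leave to an analysis plan. Where prognostic factors are candidates, the screened HR performed as well as the fixed one in the simulation. Much of this stands, and it rules out four stronger readings.

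- A reader might infer that the trial's key estimate is data-driven. The article never calls the adjusted HR primary; the fault is that it names neither HR.
- A reader might infer that baseline FPG could well be screened out and the adjusted HR biased by 4% to 8%. A factor strong enough to cause that shift would almost surely pass, so the 4% to 8% describes the unadjusted HR.
- A reader might infer that arm itself could be screened out. The same section promises an adjusted HR for arm, so this reading is strained; the wording is merely loose.
- A reader might take BMI of 25 or more in 37.5% of control men against 40.8% of intervention men (Table 3) as proof of imbalance. Women show 29.8% against 30.4%. Both sexes together give 546/1504 = 36.3% against 522/1336 = 39.1%, p = 0.13 even ignoring clustering, which is compatible with chance. FPG balance is asserted in the text, but Table 2 as available has no FPG row.

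What the reply does not answer is that a selection rule has been stated, rather than left to a later document, and that it contains no forced factor and no stratum.

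**Conclusion.** The point holds as an inexpensive improvement to a stated rule, not as evidence that the main result is invalid. Three things stand. First, the adjusted HR has an outcome-selected covariate set, in which membership of weaker factors is largely a matter of chance (35% to 72% at assumed HRs of 1.1 to 1.15 per SD), although the effect of any one of them on the arm HR is small. Second, the randomisation strata do not appear in the described analysis. Third, the main HR is unnamed, while the unadjusted analysis has no protection against imbalance from open recruitment after allocation; the shift is about 4% to 8% under the assumed imbalance and prognostic strength. The pass rates also depend on the planning event rates. The simulation presupposes that FPG is a candidate and arm is retained, neither of which the text states outright.

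**What to change.** Before unblinding, amend the Statistical analyses section as follows:

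- State which HR for arm is the main estimate.
- Estimate the confirmatory adjusted HR from the LWA/Cox model with arm always retained, a fixed set of baseline covariates (FPG as a continuous variable, age, sex and BMI) and the randomisation strata. Say whether strata enter as covariates or as separate baseline hazards, with a rule for any stratum that contains participants from only one arm.
- Report the unadjusted HR beside it, whatever the two show.
- Confine the p<0.1 screen to an exploratory analysis of risk factors, labelled as such.

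The cost is wording. The covariates are already collected, the Table 3 footnote reports only five participants excluded for missing data, and the sample size is unchanged. The change does not remove bias from unmeasured differences between those who volunteered in each arm, such as motivation, and the report should say so.

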### Follow-up and outcome

Participants will be followed up over a three- year period using data from an annual health checkup and a questionnaire regarding health and lifestyle. The questionnaires are mailed out to the participants from the lifestyle support center with self-addressed envelopes. If a completed questionnaire is not sent back to the lifestyle support center within two weeks, the lifestyle support center will contact the participant first by mail and then by telephone. We made a manual for this process. The primary outcome is the development of diabetes in participants whose FPG concentration is 100-125 mg/dL (5.6-6.9 mmol/L) at baseline. The development of diabetes is defined as; #1) a rise in FPG to a level equal to or greater than 126 mg/dL (7.0 mmol/L) as revealed in the follow-up annual health checkup, and #2) a diagnosis of diabetes or use of anti-diabetic drugs as reported in the annual questionnaire with confirmation by referring to medical records. Other outcomes are changes in body weight, BMI, plasma glucose, blood pressure, serum lipids, HbA1c, the percentage of subjects with the Metabolic Syndrome, lifestyle, and the development of cardiovascular diseases.

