### Limitations

This study has several potential limitations. One is that we identified high risk subjects using fasting plasma glucose. We will follow them as to the development of diabetes using fasting plasma glucose determined at annual health checkups and a questionnaire. We do not add any other biochemical examinations such as the oral glucose tolerance test. Therefore, we may miss diabetic subjects having normal fasting but elevated 2 h plasma glucose levels [57-59]. We may also miss subjects with IGT, IFG and IGT, both associated with a substantially increased risk of developing diabetes, are considered to be of a different entity. In the majority of populations thus far studied, IGT is more prevalent than IFG. Thus, we must be careful in interpreting results. It is possible that the efficiency of identifying high-risk subjects will be increased by combining FPG and HbA1c data [60]. This study used results obtained in 2006 annual health checkups as baseline data. At that time, only 58.5% of participating checkup sites included the measurement of HbA1c as a health checkup item. Second, the present study lacks information on the use of drugs, such as fibrate, nicotinic acid, and fish oil, which affect the metabolism of HDL-cholesterol and triglycerides. This may have led us to underestimate the prevalence of the Metabolic Syndrome. Third, participants were predominantly from workplaces. We did not succeed in recruiting more participants from communities. Since men outnumber women in many workplaces in Japan, the study population was predominantly male. This bias may limit the generalizability of our results.

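### Continuous secondary outcomes are compared as changes with no baseline covariate, by a test that depends on the distribution; a prespecified baseline-adjusted model would be a small, free improvement

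*Protocol article*

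**What the plan says.** Under Follow-up and outcome, the secondary outcomes are defined as changes: "Other outcomes are changes in body weight, BMI, plasma glucose, blood pressure, serum lipids, HbA1c". The values come from routine checkups: "Participants will be followed up over a three- year period using data from an annual health checkup". Limitations confirms the baseline source: "This study used results obtained in 2006 annual health checkups as baseline data".

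Under Statistical analyses, the arms are compared on continuous variables by Student's t-test, "or Mann-Whitney U-test according to the frequency distribution of the variable) will be used to compare the means" or, in the rank version, the distributions. No covariate enters this comparison. Covariate adjustment is stated only for the diabetes endpoint: "Cox regression analysis will be used to calculate the unadjusted and adjusted HRs and 95% CIs for arm and risk factors". The same section adds: "We do not adjust for the clustering effect for analysis of the secondary outcome".

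**The concern.** When the regression slope b of follow-up on baseline is below 1, a participant who starts high tends to show a larger fall, whatever the arm. A share (1 - b) of any baseline difference between arms then appears as a difference in change.

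This trial cannot simply rely on balance. Cluster randomization (Discussion) says that participants were recruited after their groups had been allocated, that neither they nor the recruiters were blinded, and that selection bias needs attention.

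The unadjusted change score also has a larger variance than a baseline-adjusted comparison of the same data. And letting the distribution decide between a t-test and a rank test leaves open whether the result is a mean difference or a rank shift.

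At stake are precision and some protection against imbalance in the outcomes that show whether telephone coaching altered weight, glucose and other risk factors. The primary diabetes endpoint is not affected.

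**Working it through.** The article states no power or sample size for any secondary outcome, so there is no figure of its own to reproduce here.

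**Inputs.** Participants followed for the primary outcome: 1504 control and 1336 intervention (Results). BMI interquartile ranges: 22.3-25.8 and 22.3-26.3 (Table 2). FPG entry window: 100-125 mg/dL (Inclusion and exclusion criteria). The correlation r between baseline and follow-up is not given and is assumed over a range. Clustering is ignored throughout.

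**1. Outcomes not truncated at entry.** Take equal variance at baseline and follow-up, scaled to 1.

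- Variance of a change score: 2(1 - r)
- Variance after baseline adjustment: 1 - r²
- Ratio, adjusted to change: (1 + r)/2, so the reduction is (1 - r)/2

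| assumed r | change | adjusted | reduction |
|---|---|---|---|
| 0.9 | 0.20 | 0.19 | 5% |
| 0.8 | 0.40 | 0.36 | 10% |
| 0.7 | 0.60 | 0.51 | 15% |
| 0.5 | 1.00 | 0.75 | 25% |

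**2. What this means for detectable differences.** The standard-error factor is √(1/1504 + 1/1336) = 0.0376. At 80% power and two-sided 5%, the multiplier is 1.960 + 0.842 = 2.802. At r = 0.7 the detectable difference is 2.802 × 0.0376 × √0.60 = 0.082 SD for the change score and 2.802 × 0.0376 × √0.51 = 0.075 SD after adjustment.

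For BMI, an approximate SD is the average of 3.5/1.349 and 4.0/1.349, which is 2.78. For an assumed true difference of 0.2 kg/m² at r = 0.8, power is 86% with the change score and 89% with adjustment. At r = 0.5 it is 48% and 60%.

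**3. FPG.** Selecting people on the baseline value leaves the slope b and the residual variance unchanged but shrinks the baseline variance. So Var(change) = residual variance + (1 - b)² × Var(baseline), and adjustment removes only the second term.

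As an illustration, assume bivariate normality, an untruncated r of 0.7 and an entry window of +0.5 to +2.5 SD.

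- Baseline variance inside the window: 0.213
- Residual variance: 1 - 0.49 = 0.51
- Var(change): 0.51 + 0.09 × 0.213 = 0.529
- Reduction from adjustment: 1 - 0.51/0.529, about 4%

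The in-sample r falls to 0.41, and (1 - r)/2 would wrongly suggest about 30%. Starting from r = 0.5, the reduction is about 7%, against 37% from the formula.

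**4. Carry-over of baseline imbalance.** Median BMI is 24.0 in control and 24.2 in intervention (Table 2). With an assumed slope of 0.8-0.9, a difference of 0.2 kg/m² carries 0.2 × (0.1 to 0.2) = 0.02-0.04 kg/m² into the change. The direction would favour the intervention arm.

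**5. Choosing the test by the distribution.** Simulations with 1504 and 1336 independent subjects, under normal, lognormal and heavy-tailed data, gave a type I error of about 0.049-0.054 when a normality test decided between the t-test and Mann-Whitney. No inflation was seen.

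**The case against.** The strongest reply is that this is a refinement. The outcomes are defined as changes, so the baseline is already used. For weight and BMI a high r is plausible, and the further gain is then 5-10% of variance. Results reports no difference between arms in age, sex, FPG or BMI. If recruitment after allocation was selective, adjusting for one baseline value need not remove the bias. All of this stands, and it sets the priority of the point.

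Several stronger readings are tempting and are not supported:

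- **The baseline is wasted.** It is not; it enters by subtraction.
- **FPG gains most because entry was restricted to a narrow window.** The direction is the opposite, as step 3 shows.
- **The results will be biased.** Only a route for imbalance is shown. The one figure available, for BMI, is a few hundredths of a kg/m².
- **Choosing the test by the distribution inflates false positives.** The simulations do not show this. The article also does not say that the choice waits for follow-up data, and final analysts are blinded (Blinding). What remains is that the quantity estimated is not fixed.
- **The annual values are analysed one year at a time.** The article does not say so. Time point and longitudinal modelling may be settled in an analysis plan not shown. Nor were the follow-up values all in hand when the article was written.

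The decision not to adjust secondary outcomes for clustering is a separate and larger matter. At the article's own ICC of 0.02 and cluster size of 60, the design effect is 1 + 59 × 0.02 = 2.18, and a nominal 5% test has a type I error of about 18%. The precision figures above borrow nothing from that.

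**Conclusion.** The point holds in a limited form. The article fixes an unadjusted two-sample comparison of change scores, with the test depending on the distribution, where a baseline-adjusted model would be more precise and less exposed to baseline imbalance. For outcomes not truncated at entry the variance saving is about 5-25% for r from 0.9 to 0.5. This rests on assumed correlations, equal variances at baseline and follow-up, and no allowance for clustering. For FPG the saving is smaller, about 4-7% in the truncation example. It is a low-priority improvement to supportive outcomes.

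**What to change.** Analyse each continuous secondary outcome with a linear model that contains arm, the 2006 baseline value and randomisation stratum, with group as a random effect. Add participant as a random effect if years 1-3 are modelled together. Report adjusted mean differences with 95% confidence intervals. Fix any transformation in advance, for example the logarithm for triglycerides, instead of letting the distribution choose the test.

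The 2006 values precede allocation, which began in March 2007, so they are valid covariates. A change score already needs the same baseline value, so the adjusted model excludes nobody further, including for HbA1c, which only 58.5% of checkup sites measured in 2006. The cost is a revised paragraph of analysis text and standard code; no new data are needed.

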### Retention

The final sample size (2840 participants) would provide >80% power to detect a 50% reduction in the rate of development of T2DM among participants assigned to the lifestyle intervention with a 5% level of significance (two-sided), after no adjustment for losses in follow-up. The follow-up of participants is scheduled to finish in March 2012. Retention of participating health checkup facilities and subjects are critical for the success of this study. Drop-out rates are generally high in lifestyle programs conducted in primary healthcare clinical settings. To secure enough samples for analysis, participants are encouraged to attend an annual health checkup through a letter from the lifestyle support center. The lifestyle support center gives safety advice to prevent sport injuries which could lead to dropping out of the study.

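### Secondary outcomes are to be tested without allowing for clustering in a cluster-randomised trial; at the protocol's own ICC of 0.02, a nominal 5% test has a true size of about 16% to 21%

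*Protocol article*

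**What the plan says.** Under Randomization, the protocol article allocates 43 groups, 22 to intervention and 21 to control. Under Sample size, it inflates the individually randomised sample size for clustering: "When the ICC and the cluster size (number of individuals in each cluster) are assumed to be 0.02 and 60".

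Under Statistical analyses, the two tiers of outcome are treated differently. For the first: "We will take into account the clustering effect in the main outcome analysis and sub-analysis using the LWA model". For the second: "We do not adjust for the clustering effect for analysis of the secondary outcome". No reason is given for the difference.

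The same paragraph names the comparisons. Student's t-test or the Mann-Whitney test "will be used to compare the means (or the distribution) of the two study arms for continuous variables". For proportions: "Chi-square test or chi-square for trend will be used to compare proportions for categorical variables". The threshold is common to all: "A p value less than 0.05 is considered significant". The Retention section describes the 5% level as two-sided.

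The outcomes concerned are listed under Follow-up and outcome: "Other outcomes are changes in body weight, BMI, plasma glucose, blood pressure, serum lipids, HbA1c". The list goes on to the proportion with the Metabolic Syndrome, lifestyle, and incident cardiovascular disease.

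**The concern.** A test that ignores the unit of randomisation is valid only if the ICC is zero. The protocol does not believe that: its sample size more than doubles to pay for within-group correlation. The article also gives reasons to expect correlation in the secondary outcomes. Weight and blood pressure are measured at the check-up sites, and blood is analysed in clinical laboratories with no added study tests (Health checkups). Members of a group share a workplace or community, which is the stated reason for randomising clusters (Discussion, Cluster randomization). Each group is managed by a single support company (Lifestyle intervention).

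If the correlation is ignored, standard errors are too small and p values too low. A difference in weight, glucose, lipids or Metabolic Syndrome prevalence could then be declared significant at a threshold that is not 5%.

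This is a rule written into the current text, not a detail left to a fuller analysis plan.

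**Working it through.** **1. Reproduce the plan's own figures (Sample size section).** Inputs: N = 1100, ICC = 0.02, cluster size m = 60, dropout 30%.

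- Design effect: DE = 1 + (60 − 1) × 0.02 = 2.18
- S = 2.18 × 1100 = 2398
- Clusters: 2398 / 60 = 39.97, i.e. 40
- With dropout: 2398 / 0.70 = 3426

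All agree with the article.

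**2. Cluster sizes to use.** The Results section gives 1504 + 1336 = 2840 participants for the main analysis. Three of the 43 groups enrolled nobody with a fasting value, which leaves 40. The enrolled mean is 2840 / 40 = 71. After 30% dropout it is 71 × 0.70 = 49.7, about 50.

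**3. True size of an unadjusted test.** Under the null, the usual test statistic has variance DE instead of 1. Hence:

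- true size = 2 × [1 − Φ(1.96 / √DE)]
- width of an unadjusted 95% interval relative to the proper width = 1 / √DE

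At ICC 0.02 with equal clusters:

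| m | DE | 1.96/√DE | True size | Interval width ratio |
|---|---|---|---|---|
| 50 (after dropout) | 1.98 | 1.39 | 16.4% | 0.71 |
| 60 (planned) | 2.18 | 1.33 | 18.4% | 0.68 |
| 71 (enrolled mean) | 2.40 | 1.27 | 20.6% | 0.65 |

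A simulation of the t-test with 40 clusters of 60 (10,000 replicates) gave 18.2%, against 18.4% from the formula.

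**4. Sensitivity to the ICC.** The article gives no ICC for any secondary outcome. The values below, other than 0.02, are assumptions, at m = 60 with equal clusters.

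| ICC | DE | True size |
|---|---|---|
| 0.001 | 1.059 | 5.7% |
| 0.005 | 1.295 | 8.5% |
| 0.01 | 1.59 | 12.0% |
| 0.02 | 2.18 | 18.4% |
| 0.05 | 3.95 | 32.4% |

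**5. Unequal clusters.** Results reports median sizes of 61 (interquartile range 35–88) in control and 60 (41–94) in intervention. A coefficient of variation of 0.6 is roughly consistent with these, but is an assumption. With DE = 1 + [(1 + CV²) × m − 1] × ICC and m = 71:

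- DE = 1 + (1.36 × 71 − 1) × 0.02 = 2.91, true size 25.1%

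The same CV gives 22.5% at m = 60 and 20.0% at m = 50.

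**6. Allocation within divisions.** The Randomization section says that where a health care division formed two or more groups, these were placed in both arms. The simulation was repeated with 20 pairs of groups, one of each pair per arm, at ICC 0.02. The share of between-group variance common to the pair was varied; unequal sizes used an assumed CV of 0.65.

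| Share common to the division (assumed) | Equal sizes of 60 | Unequal sizes |
|---|---|---|
| None | 18.2% | 25.5% |
| Half | 12.3% | 18.8% |
| All | 4.6% | 11.2% |

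This is a best case for the pairing, because divisions with a single group gain nothing from it.

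**The case against.** The strongest reply has three parts.

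- **The ICC was assumed for diabetes incidence.** The outcomes in question are quite different from one another, and some change scores may have a much smaller ICC. This stands. It makes the 16% to 21% conditional, and near ICC 0.001 the inflation is negligible.
- **Within-division allocation balances part of the shared environment.** This also stands, and step 6 shows the inflation shrinking. It disappears only if all between-group variance lies at division level, every division is paired and cluster sizes are equal. The reported sizes are not equal, some divisions formed only one group, and the protocol's sample size formula takes no credit for the pairing.
- **These are secondary outcomes.** True, and the main outcome and sub-analysis are covered by the LWA model. But rank does not make an invalid p value valid, and the plan applies the same 0.05 threshold.

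Three stronger readings might be inferred and are not supported:

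- **That the error rate simply is 20%.** The article contains no ICC that would establish this for any secondary outcome.
- **That the plan prescribes intervals that are too narrow.** The Statistical analyses section mentions 95% intervals only for hazard ratios, so the width ratio applies to any unadjusted interval that may be reported for a secondary outcome. Nor does the section say which test cardiovascular events will receive.
- **That the tests wrongly ignore a 2006 baseline available for every outcome.** The listed outcomes are largely changes, so baseline already enters; conditioning on it is a separate matter of efficiency. Nor does every outcome have such a value: 58.5% of sites measured HbA1c in 2006 (Limitations), lifestyle comes from the recruitment questionnaire, and cardiovascular disease is an incident event.

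**Conclusion.** The rule is wrong as written. It sets aside the unit of randomisation for every outcome beyond the main outcome and sub-analysis, against the protocol's own assumption of a positive ICC, and gives no reason.

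The headline range of about 16% to 21% rests on ICC 0.02, equal clusters of 50 to 71 and no gain from within-division allocation. An unadjusted 95% interval reported under the same assumptions would have 0.65 to 0.71 of its proper width. Departures run both ways: about 25% with unequal clusters (m = 71, CV 0.6), and lower with a smaller ICC or where pairing within divisions removes between-group variance. The direction is firm for any appreciable between-group variance that the allocation does not balance; the exact size for each outcome is unknown until its ICC is estimated.

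The conclusion on the primary outcome is untouched by this point.

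**What to change.** Delete the sentence that exempts the secondary outcomes, and state that they will be analysed by a method that accounts for the randomised group. Suitable choices are a mixed model with a group effect, GEE with a small-sample correction (about 40 clusters), or an analysis of cluster-level summaries. Time-to-event outcomes can use the LWA model already named for the main outcome.

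If the sponsor prefers to keep unadjusted comparisons, the minimum change is to label them descriptive and report them without p values or claims of significance.

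No new data are needed. The cost is routine programming and wider intervals: at ICC 0.02 with equal clusters, by a factor of √1.98 = 1.41 to √2.40 = 1.55 over the unadjusted ones.
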